#### Standardized patient (SP) interview methodology

Measurement of participant performance in simulated sessions with the standardized patient was used to assess actual skills acquisition. The goal was to create an assessment protocol that ensured standardization of stimulus conditions while permitting actors in the standardized patient role to respond with considerable flexibility depending upon which of a wide range of provider behaviors occurred. The standardized patient interviews were conducted at baseline and follow-up for all participants.

Participants received email orientation materials 72 h prior to their interview. This orientation included a brief description of procedures for the standardized patient interview, description of the clinical background of the patient, information about the time and date of the phone interview, and the phone number at which they would be contacted. 24 h prior to the scheduled interview, the actor was instructed to call the participant and remind him or her to read the materials and confirm when the interview would take place. If the participant did not answer this call, the actor was instructed to leave a voicemail or a message with the receptionist if voicemail was not available.

Simulated interviews were conducted during 50-minute telephone calls. The 50-minute sessions were divided into a five-minute introduction/orientation followed by three 15-minute segments (one for each intervention). We defined a segment as a portion of the standardized patient interview that could be rated according to study criteria.

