#### Statistical analysis plans

##### Primary analyses

The primary outcome of the study intervention is the performance of participants in demonstrating CBT techniques during the SPI assessment at post-training. Summary scores for each of the CBT techniques will be constructed from the ratings of the SPIs and the properties of the scores evaluated. The analyses to be performed will compare the performance of participants in the training-as-usual (control) and web-based training groups using the analysis of covariance (ANCOVA) comparing the average post-test scores among the three training groups, adjusting for baseline scores [31]. We hypothesize that participants in the web-based training groups will exhibit greater improvement in skills performance than those in the training-as-usual (control) group. We also hypothesize that web-based training plus supervision will be associated with greater skills improvement than web-based training alone. If the null hypothesis of no difference among the three groups is rejected, we will compute pre-planned comparisons of the scores between the individual groups adjusting for multiple comparisons. All participants will be analyzed in the training group to which they were randomly assigned, regardless of their compliance with the assigned training method and the assessments. Participants who do not complete the post-training SPI will be considered to have the same value at post-test as at baseline. To assess sensitivity of our results to potential response bias due to more ‘successful’ trainees completing the follow-up assessment, we assumed that non-completers made no change from baseline (last observation carried forward). This is a commonly used method of imputation when doing this type of sensitivity analysis.

Analyses focusing on the intent-to-train sample will also be repeated for the sample of participants who completed ‘therapeutic doses’ of the training interventions. To meet the criterion for completion of the web portion of the training, a participant will have to complete 75% of each of the three modules. To complete the web-based training plus supervision process, a participant will have to complete 75% of each of the online modules and attend three or more of the supervision sessions.

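### As written, baseline carried forward is both the primary rule for a missing post-training standardized patient interview and the sensitivity analysis, so the check cannot differ from the result

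*Protocol article*

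**What the plan says.** All statements are in the Protocol article.

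- **Outcome and model** (Primary analyses): "The primary outcome of the study intervention is the performance of participants in demonstrating CBT techniques during the SPI assessment at post-training", compared by "analysis of covariance (ANCOVA) comparing the average post-test scores among the three training groups, adjusting for baseline scores".
- **Analysis set** (same section): everyone is analysed as randomised, "regardless of their compliance with the assigned training method and the assessments".
- **Rule for a missing post-training SPI** (same section): "Participants who do not complete the post-training SPI will be considered to have the same value at post-test as at baseline".
- **Sensitivity analysis** (the next sentence): the assumption made is "we assumed that non-completers made no change from baseline (last observation carried forward". The purpose given for it is to guard against selective return of the better trainees for the second SPI.
- **Other repeat analysis** (same section): the intent-to-train analyses "will also be repeated for the sample of participants who completed ‘therapeutic doses’ of the training interventions". The dose is 75% of each of the three modules and, for the supervised group, at least three supervision sessions as well.
- **Number of SPIs** (Standardized patient (SP) interview methodology): "The standardized patient interviews were conducted at baseline and follow-up for all participants".

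**The concern.** A sensitivity analysis is useful only if it changes the assumption under test. Here the assumption is that a participant without a second SPI would have scored exactly what they scored at baseline. The primary rule makes that assumption and the check makes it again.

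The assumption also sits badly with the trial's hypothesis. The plan expects trained participants to improve, yet a trained participant who misses the second SPI is given zero gain, even if all modules were completed.

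Unequal missingness is plausible by design. Under Recruitment and randomization, the supervised group has up to six extra calls. Both web groups meet the continuing-education quiz at the midpoint assessment, before the second SPI. Controls get the training and the credits only after the final assessment. If completion differs by arm, the rule carries that difference into the treatment contrasts. Supervision versus web training alone is the most exposed, because its expected difference is the smallest.

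**Working it through.** **1. Are the two rules the same?** The SPI is measured at baseline and once afterwards. For anyone without the second SPI, the last observation is the baseline SPI. Both rules set post = baseline for the same people, enter the same ANCOVA and return the same estimate. This needs no missing rate.

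**2. Does the therapeutic-dose repeat vary the assumption?** Membership depends on modules completed and sessions attended. A participant can meet the dose and lack the second SPI, or have the SPI and miss the dose. The repeat changes who is analysed, not how a missing SPI is treated.

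**3. The article's own figures.** Power analysis: 40 per group, 2.5% level; 48% v 15% gives 79% power and 54% v 15% gives 91%. A two-sided Fisher exact calculation gives 78.8% and 91.3%, so these figures reproduce. They are used below only as a scale, because the primary analysis is of scores, not success rates.

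**4. Equal missingness d in all arms.** Assumptions: missing completely at random, and a baseline success rate of 15% (no change in control). The carried-forward rate is p(1 − d) + 0.15d, so the difference from control is (p − 0.15)(1 − d). At d = 20%: 33 × 0.8 = 26.4 points and 39 × 0.8 = 31.2 points.

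The article's text gives no missing rate, so d is a range. The 11% row is what 1 − 120/135 would imply if the gap between the recruitment target and the powered sample were a dropout allowance, which the article does not say.

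| d | Difference from control: web / supervised (points) | Power, 40 randomised per arm, carried forward | Power, 40 per arm, observed only | Power, 56 per arm, carried forward |
|---|---|---|---|---|
| 0 | 33.0 / 39.0 | 78.8% / 91.3% | 78.8% / 91.3% | 92.5% / 98.2% |
| 11% | 29.4 / 34.7 | 67.8% / 83.1% | 73.7% / 87.4% | 85.2% / 94.8% |
| 20% | 26.4 / 31.2 | 57.4% / 73.6% | 66.0% / 82.0% | 76.5% / 89.3% |
| 30% | 23.1 / 27.3 | 45.2% / 60.7% | 58.2% / 74.6% | 64.1% / 79.4% |

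Table 1 gives 56, 57 and 55 randomised, so the last column is close to the actual trial.

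On a continuous scale, a simulated three-arm ANCOVA (56 per arm, baseline–post correlation 0.5, random missingness, no change in control) turned a true 0.50 SD effect into 0.45, 0.40 and 0.35 SD at 10%, 20% and 30% missing. ANCOVA on observed cases stayed at 0.50.

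**5. Unequal missingness, supervision minus web.** The true difference on the article's rates is 54 − 48 = 6 points.

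- 30% missing with supervision, 10% with web: (0.54 × 0.7 + 0.15 × 0.3) − (0.48 × 0.9 + 0.15 × 0.1) = 0.423 − 0.447 = −2.4 points.
- Reversed: 0.501 − 0.381 = +12.0 points.
- 20% in both: 0.462 − 0.414 = 4.8 points.

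**6. Training versus control with a gain g in every arm.** For true effect e, the carried-forward contrast is (1 − d_T)(g + e) − (1 − d_C)g.

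- Assumed 10/20/30% missing (control/web/supervised), g = 0.2 SD, e = 0.5 and 0.7 SD: web 0.8 × 0.7 − 0.9 × 0.2 = 0.38; supervised 0.7 × 0.9 − 0.9 × 0.2 = 0.45; supervised minus web 0.07 (true 0.2).
- Same rates and g, but supervision adds nothing: 0.7 × 0.7 − 0.8 × 0.7 = −0.07 SD.
- 30% missing in control, 10% in web, g = 0.3, e = 0.5: 0.9 × 0.8 − 0.7 × 0.3 = 0.51, so no shrinkage.

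**The case against.** **Carry-forward may be meant only as the sensitivity analysis.** The second sentence gives that purpose, and the first could be read as defining its rule. This is a fair reading. But the first sentence directly follows the as-randomised statement and carries no such limit. If it was meant only for the sensitivity analysis, it is misplaced and the article states no primary rule. The text needs correcting on either reading.

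**Missing at random cannot be verified either.** The plan's stated worry is that the more successful trainees return. If non-completers truly did not change, then in the 10/20/30% example 0.38, 0.45 and 0.07 SD are right, and the observed-data values of 0.50, 0.70 and 0.20 are too high by 0.12, 0.25 and 0.13. This stands. It is the reason to keep no change as a sensitivity analysis, but not a reason to use it in both roles.

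**The rule is conservative.** This is true for training versus control under equal missingness. It is not assured for supervision versus web, which the article hypothesises about in the same section.

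Three stronger readings are tempting, and the document does not support them:

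- A reader might infer that the primary estimate is biased as a matter of fact. That requires missing second SPIs and non-completers who did change. The text shows neither, and the completion flowchart is not available.
- A reader might infer that both control contrasts must shrink. The last line of the working is a counterexample.
- A reader might infer that no analysis anywhere would reveal a problem. The dose-completer repeat could give an indirect signal, and a condensed article cannot show what a full analysis plan contains.

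**Conclusion.** The circularity is certain from the text and depends on no assumed rate: as written, the sensitivity analysis must return the primary result, and the therapeutic-dose subset is not a clean substitute for it.

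The bias is conditional on missing second SPIs and on real change among non-completers, which the trial hypothesises for its trained arms. Under those conditions and equal missingness, training-versus-control effects are multiplied by one minus the missing rate. That is modest at about 10% missing and substantial at 30%. Under unequal missingness the bias can go in either direction; supervision versus web could range from −2.4 to +12.0 points around a true 6 when the two rates are 30% and 10%.

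All of these are illustrations over an assumed range. No size can be given for this trial, and any power or interval coverage computed under a particular missingness pattern describes that scenario, not the plan.

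**What to change.** 1. Name one primary analysis that is valid under missing at random. The simplest is the planned ANCOVA on observed post-training SPIs, adjusting for baseline score and CBT-expertise stratum. The alternative is multiple imputation by arm using baseline SPI, stratum and training completion, followed by the same ANCOVA. The second also allows missingness to depend on training completed.
2. Keep no change from baseline as the named sensitivity analysis for selective completion, and state that it is not the primary rule.
3. Optionally add a reference-arm imputation, in which trained non-completers are imputed from the control group.
4. Report second-SPI completion by arm beside the estimates.

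The Discussion implies the study was still blinded when the article was written, so the choice should be fixed and dated before unblinding. The cost is analysis wording, some programming, and slightly wider intervals than single imputation gives. No new data are needed.

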##### Secondary analyses

We also hypothesize that providers in the web-based training groups will show significantly greater improvement in CBT-related knowledge, perceived self-efficacy, and self-reported implementation of CBT techniques than those in the training-as-usual (control) group. The baseline and post-test assessments consist of multiple choice knowledge items, perceived self-efficacy, and practice behavior variables. As with the SPI scores, summary scores will be calculated from the individual questions. Treatment groups will be compared using ANCOVA on the post-test scores controlling for the baseline scores with follow-up comparisons as described above. Moderator analyses are not planned given the use of a randomized trial for testing the primary and secondary hypotheses of the study.

##### Power analysis

Power calculations were computed based on the estimated percentage of participants who would successfully implement the techniques as assessed by the SPI. These calculations indicated that 40 participants per group (total n = 120) would provide 79% power to detect a rate of successful implementation of 48% in the web-based training (without supervision) group compared to 15% in the training-as-usual (control) group, and 91% power to detect a rate of 54% in the web-based training plus supervision group compared to 15% in the training-as-usual (control) group, both at the 2.5% significance level.

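### The stated 79% and 91% power are correct for a success/failure test that the plan does not run, and the supervision-over-web hypothesis has no stated power and almost none on the plan's own rates

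*Protocol article*

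**What the plan says.** The Power analysis section rests on a binary quantity: "Power calculations were computed based on the estimated percentage of participants who would successfully implement the techniques as assessed by the SPI". With 40 per group it claims "79% power to detect a rate of successful implementation of 48% in the web-based training (without supervision) group compared to 15" per cent under control, and for the supervised arm "91% power to detect a rate of 54% in the web-based training plus supervision group compared to 15% in the training-as-usual (control) group". One level is set for the pair of contrasts: "both at the 2.5% significance level". Only these two contrasts are given.

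The Primary analyses section describes something else. "Summary scores for each of the CBT techniques will be constructed from the ratings of the SPIs", and the groups are compared by "analysis of covariance (ANCOVA) comparing the average post-test scores among the three training groups, adjusting for baseline scores". If the three-group null is rejected, comparisons between individual groups follow, adjusted for multiplicity by a method the article does not name. Next to the hypothesis of web training over control stands a second one: "web-based training plus supervision will be associated with greater skills improvement than web-based training alone".

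Neither the primary nor the secondary analyses include a comparison of success proportions. Table 1 gives 56, 57 and 55 randomised to control, web, and web plus supervision (19+37, 21+36, 19+36), 168 in all.

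**The concern.** The power statement and the primary analysis differ in three ways.

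- **Endpoint and test.** Power is for a proportion of successes. The analysis compares mean scores adjusted for baseline.
- **Set of comparisons.** A 2.5% level is 5% divided by two and matches the two contrasts listed. Three groups and the stated hypotheses give three pairwise contrasts.
- **Hypotheses covered.** The supervision hypothesis is part of the primary analyses but is absent from the power paragraph.

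The third difference matters most. The Background says that evidence for post-training supervision is not strong, and the Discussion asks about web training with and without supervision as its central question. If the planning rates are taken at face value, the supervision contrast will very probably be non-significant even when supervision helps exactly as much as those rates imply. Without a warning, such a result could be taken as evidence that supervision adds nothing.

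**Working it through.** **Inputs.** Rates 15% (control), 48% (web) and 54% (web plus supervision), 40 per group and level 0.025, all from Power analysis. Randomised numbers 56/57/55 from Table 1. Assumptions not in the article: two-sided testing, a latent-normal score, the baseline correlation r, and a Bonferroni level of 0.05/3 = 0.0167 as one possible adjustment.

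**Step 1: reproduce the stated power.** Sum the binomial probabilities of all pairs of counts (x1, x2) for which the test rejects, with n = 40 per group and level 0.025:

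| Test | 15% vs 48% | 15% vs 54% |
|---|---|---|
| Stated | 79% | 91% |
| Fisher, two-sided | 78.8% | 91.3% |
| Yates-corrected chi-square | 78.8% | 91.3% |
| Uncorrected chi-square, exact enumeration | 84.9% | 94.5% |
| Fisher, one-sided | 86.1% | 94.9% |

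The stated figures match a two-sided Fisher or Yates-corrected test. The article names no test, so this is inferred from the match.

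**Step 2: supervision versus web on the same rates, binary scale.** Two-sided Fisher, 48% vs 54%, level 0.025: 3.6% at 40 per arm and 4.2% at 56 per arm. The uncorrected normal approximation gives 4.4% and 5.4%. For 80% power:

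n = [2.241·√(2·0.51·0.49) + 0.842·√(0.48·0.52 + 0.54·0.46)]² / 0.06² ≈ 1,319 per arm.

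**Step 3: move to the planned scale.** Suppose success means that a normal score with common SD exceeds a fixed cut-off. Differences in SD units are then differences of normal quantiles. The quantiles are −1.036 (15%), −0.050 (48%) and 0.100 (54%), so:

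- web vs control: 0.986 SD
- web plus supervision vs control: 1.137 SD
- web plus supervision vs web: 0.151 SD

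For ANCOVA the standardised contrast is λ = d / √(2(1 − r²)/n), and power ≈ Φ(λ − z) + Φ(−λ − z), with z = 2.241 at 0.025 and 2.394 at 0.0167.

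*Control contrasts.* The least favourable case is d = 0.986, n = 40, r = 0. Then λ = 0.986/0.2236 = 4.41 and power is 98.5% at 0.025 or 97.8% at 0.0167 (97.5% with the t distribution). Every other case is higher.

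*Supervision vs web, d = 0.151:*

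| n per arm | Level | r = 0 | r = 0.5 | r = 0.7 |
|---|---|---|---|---|
| 40 | 0.0167 | 4.3% | 5.3% | 7.3% |
| 40 | 0.025 | 5.8% | 7.2% | 9.7% |
| about 56 | 0.0167 | 5.5% | 7.0% | 10.0% |
| about 56 | 0.025 | 7.4% | 9.3% | 12.9% |

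These are powers of the pairwise contrast alone. Requiring the three-group test to reject first cannot raise them.

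**Step 4: what the randomised numbers can detect.** With 56 per arm and 80% power (t distribution), the detectable difference at levels 0.025 to 0.0167 is 0.59–0.62 SD for r = 0 and 0.51–0.53 SD for r = 0.5. Scaling the latter by √(0.51/0.75) = 0.825 gives about 0.42–0.44 SD for r = 0.7. The supervision difference implied by the planning rates is 0.15 SD.

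**The case against.** The arithmetic in the power paragraph is sound. A reader might infer that 79% and 91% are miscalculated. They are not, and the fault is only that they belong to another test.

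A reader might also infer that the trial is too small for its main question. The documents do not support that. Sizing on a dichotomised version of the same performance is cautious, and the control contrasts are probably better powered than stated.

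It is tempting to say that allowing for three comparisons lowers the power to 73.7% and 88.1%. Those are the Fisher figures at 0.05/3 with 40 per arm. The adjustment rule is not named, and a significant three-group test followed by 5% pairwise tests would control the error rate for a single score, with Fisher power of 86.1% and 94.9% at 40 per arm. At 0.05/3 with the realised 56 per arm, Fisher power is 90.2% and 97.4%. No loss of power is established.

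Nor is any power misreported for supervision versus web, because none is claimed. The 48% and 54% are given as rates to detect against control, and six points is never called the expected benefit of supervision. The cut-off for success, the adjustment rule and the SD may stand in the full protocol.

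All of this stands, and it limits the point to one of description and interpretation. It does not remove it: the article gives a power basis that differs from its own primary analysis and leaves one hypothesis of that analysis without any.

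**Conclusion.** The point holds as a mismatch between the power statement and the planned analysis. It is neither a calculation error nor a shortfall in sample size. The 79% and 91% are correct for a two-sided Fisher-type test of success rates in two control contrasts, and they are not properties of the planned ANCOVA. For the control contrasts the practical effect is probably nil, with ANCOVA power of about 97% or more at 40 per arm. The supervision-over-web hypothesis is essentially unpowered if the planning rates are the true ones: about 4% on the binary scale at the 2.5% level, and about 4–13% by ANCOVA. The ANCOVA figures rest on the latent-normal assumption, a common SD, a baseline correlation of 0–0.7, 40–56 per arm and a level of 1.67–2.5%. Even unadjusted at 5%, with about 56 per arm and r = 0.7, power is only about 20%. A larger true effect of supervision would raise these figures, but the article states none.

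**What to change.** Rewrite the power paragraph for the ANCOVA of the summary scores. Give power, or the difference detectable with 80% power, for all three contrasts at the randomised 56/57/55 and at the per-contrast level that the named adjustment implies. Show the baseline correlation as an assumed range; at 0.5, for example, 80% power corresponds to about 0.51–0.53 SD. The success-rate calculation can stay as the historical basis for 40 per group, labelled as such.

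Add one sentence to the limitations: supervision versus web alone will be reported as an estimate with a confidence interval, the trial was not powered for it, and a non-significant result will not be read as no added benefit.

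The cost is one rewritten paragraph and one sentence, with no change to the sample size or the analysis. The article leaves outcome results to later papers, so the statement can precede them.

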## Results and discussion

In this paper, we present evidence for the effectiveness of our study recruitment procedures. As shown in the flowchart of recruitment and study completion in Figure 9, we exceeded our recruitment goals. The study protocol called for recruitment of an approximate target of 135 mental health providers; in fact we were able to randomize 168 participants for the study, ahead of the planned recruitment pace. In keeping with the overall composition of VHA mental health providers, our sample was predominantly white (79%), female (70%), and had post-graduate training in psychology, social work, nursing or psychiatry. The average age was 49, and more than 90% had post-graduate qualifications (Master’s or Doctoral level).

